## Abstract

**Background:**

Of the 150,000 patients annually undergoing coronary artery bypass grafting, 35% develop complications that increase mortality 5 fold and expenditure by 50%. Differences in patient risk and operative approach explain only 2% of hospital variations in some complications. The intraoperative phase remains understudied as a source of variation, despite its complexity and amenability to improvement.

**Objective:**

The objectives of this study are to (1) investigate the relationship between peer assessments of intraoperative technical skills and nontechnical practices with risk-adjusted complication rates and (2) evaluate the feasibility of using computer-based metrics to automate the assessment of important intraoperative technical skills and nontechnical practices.

**Methods:**

This multicenter study will use video recording, established peer assessment tools, electronic health record data, registry data, and a high-dimensional computer vision approach to (1) investigate the relationship between peer assessments of surgeon technical skills and variability in risk-adjusted patient adverse events; (2) investigate the relationship between peer assessments of intraoperative team-based nontechnical practices and variability in risk-adjusted patient adverse events; and (3) use quantitative and qualitative methods to explore the feasibility of using objective, data-driven, computer-based assessments to automate the measurement of important intraoperative determinants of risk-adjusted patient adverse events.

**Conclusions:**

We anticipate that this project will substantially increase our ability to assess determinants of variation in complication rates by specifically studying a surgeon’s technical skills and operating room team member nontechnical practices. These findings may provide effective targets for future trials or quality improvement initiatives to enhance the quality and safety of cardiac surgical patient care.

**International Registered Report Identifier (IRRID):**

PRR1-10.2196/22536

## Introduction

### The Epidemiology of Cardiac Surgery

Nearly 150,000 coronary artery bypass grafting (CABG) procedures are performed annually in the United States, and it is a procedure associated with a high rate of major adverse events (35% of patients) that vary by hospital [1]. These adverse events increase a patient’s risk of mortality 4.7 fold and are associated with more than US $50,000 in additional health care expenditure per patient [1-4]. While understudied, intraoperative performance (including the surgeon’s technical skills and team-based nontechnical practices) is an important potentially modifiable determinant of operative adverse events (Figure 1) [5,6].

**Figure 1 figure1:**
[figure not shown]
Conceptual model.

### The Role of Technical Skills in Surgical Outcomes

Prior research has evaluated the association between technical skills (defined as “psychomotor action or related mental faculty acquired through practice and learning pertaining to a particular craft or profession” [7]) and operative outcomes [8]. While taxonomies exist to objectively and reliably assess a surgeon’s technical skills, they are often applied within simulated structured scenarios that may not mimic real-world patient care (Table 1). In one exception, investigators applied the Objective Structured Assessment of Technical Skill (OSATS) [9] to real operative settings including 10 clinician experts who rated a single 25 to 50-minute video segment of a laparoscopic operation from 20 surgeons [5]. Assessments, linked to data from the last 2 years of each surgeon’s experience, were significantly inversely associated with the surgeon’s adverse events and mortality outcomes. In another study, surgical skills were associated with outcomes from cancer surgery [10].

**Table 1 table1:** Application of the Objective Structured Assessment of Technical Skills (OSATS) to cardiac surgery.

Domains	Description	Illustrative high-quality cardiac surgical tasks
Respect for tissue	Gentle tissue handling that does not result in tissue injury	Passing a needle through a coronary artery without tearing the tissue
Time and motion	Economy of motion and maximum efficiency	Efficiency of movement for suturing proximal anastomoses
Instrument handling	Fluid use of instruments and absence of awkwardness	Fluidity of motion between the scrub nurse and surgeon (and back)
Flow of operation	Smooth transitions from one part of the operation to another	Smooth transitions from cannulation (venous and aortic) to anastomosis phase
Suture handling	Efficient knot tying using fluid motions of the hands and fingers	Tying an 8-0 or a 7-0 suture (“microsuture”) resulting in secure knots without causing tissue injury
Steadiness	Absence of tremor motions of the hands	Fine motor movement: passing a needle through a coronary artery without tearing the tissue

### The Role of Nontechnical Practices in Surgical Outcomes

Nontechnical practices (“the cognitive, social, and personal resource skills that complement technical skills, and contribute to safe and efficient task performance” [11]) are both individual and team based. While improvement in these practices has been associated with decreases in operative mortality [12], investigations thus far have focused on developing robust validated taxonomies of behavior with corresponding assessment tools customized to the individual team members’ intraoperative care role. Dominant taxonomies [13-15] include Non-Technical Skills for Surgeons (NOTSS), Anesthetists’ Non-Technical Skills (ANTS), Perfusionists Intraoperative Non-Technical Skills (PINTS), and Scrub Practitioners’ List of Intraoperative Non-Technical Skills (SPLINTS). These taxonomies enable assessments of the following four important categories of nontechnical practices: situation awareness, decision making, communication and teamwork, and leadership/task management. Situation awareness [16] is the process of developing and maintaining a dynamic awareness of the operative situation based on gathering and interpreting data from the operative environment. This domain is essential for effective decision-making [17], representing skills for diagnosing a given situation to inform a judgment about appropriate actions. Successful surgery also depends on social skills allowing multiple individuals with task interdependencies and shared goals to communicate and work effectively as a team [18]. Dysfunctional team dynamics, ineffective communication, and ambiguous leadership [19] account for a substantial proportion of operative adverse events [20].

A surgeon’s nontechnical practices, manifesting as diagnostic failure [21] or a breakdown in teamwork and information sharing [22], may contribute to a higher risk of a major adverse event or death. The largest operative study of NOTSS conducted thus far involved 715 surgical procedures and 11,440 assessments [23]. Surgeons’ nontechnical skills were rated as good (score of 4) in 18.8% of responses, acceptable (score of 3) in 49.1%, marginal (score of 2) in 21.9%, and poor (score of 1) in 0.9%. In a video-based study including 82 cardiac surgeons, there was a 129% increased odds (after adjusting for technical skills) of higher patient safety scores with every 1-point increase in the NOTSS score [6].

### Rationale for the Study

This study will evaluate how operative skills and nontechnical practices impact CABG outcomes. Patients undergoing CABG are at risk of harm due in part to the (1) reconstruction of anatomical structures under high magnification, (2) multiple high-risk phase transitions of care between team members (eg, anesthesiologist and perfusionist), and (3) need for communication and teamwork (eg, instrument handoffs) across many team members.

### Innovation

Our proposed study is novel and innovative for three important reasons. To our knowledge, this study will be the first (1) multicenter intraoperative evaluation of both technical skills and operative team nontechnical practices at scale, (2) study to relate evaluation of intraoperative nontechnical practices with important clinical outcomes, and (3) study to apply a video-understanding platform to high fidelity recorded surgical videos to assess feasibility of automated objective assessments of technical skills and nontechnical practices.

## Methods

### All Aims

Preliminary Institutional Review Board (IRB) review has been completed at the University of Michigan by the Institutional Review Boards of the University of Michigan Medical School. This study will include a single IRB to govern research activities conducted across the collaborating hospitals.

#### Study Population

Our population will include adult patients undergoing electively scheduled CABG operations using cardiopulmonary bypass performed by attending surgeons at six hospitals participating in the Multicenter Perioperative Outcomes Group (MPOG) Collaborative, a national physician-led collaborative of academic and community hospitals, and specialty-specific peer assessors. Surgeons who have operated at their hospital for less than 2 years will be excluded.

#### Digital Recording

We will record 506 CABG operations at six hospitals. The study coordinator will use a randomization protocol from the Data Coordinating Center (DCC) to select, by week, different cardiac surgical operating rooms for video recording. The coordinator will synchronize the cameras with other operating room data sources (eg, intraoperative record as submitted to MPOG) (Figure 2). Three Canon XC15 cameras will be used, with two focusing on operative team members and one focusing on the surgical team. Beyond maximizing nonobstructed visualization, camera positions have been chosen to maximize capture of team member activities and minimize obstruction of existing workflow.

**Figure 2 figure2:**
[figure not shown]
Proposed intraoperative recording configuration. OR: operating room.

Key transitions in phases of patient care are routinely documented within the intraoperative electronic health record of participating MPOG hospitals. These data are validated and mapped to universal MPOG concepts [24]. Digital recordings will be segmented based upon key transitions in phases of care; operative recordings will begin when the patient enters the operating room and end when the patient exits the operating room.

Study data will be transmitted to the DCC, which will conduct audio and video quality checks across hospitals and recordings. Initially, investigators at the DCC will review the entire recording to fine tune the MPOG event timestamping to the exact second. Given the input operative data, a Hidden Markov Model [25,26] or deep learning–based approach [27] will divide the procedure into temporal segments and associate them with the procedural step labels from the operative script. Standardized segments for assessment will only contain critical operative portions (Table 2).

**Table 2 table2:** Illustrative operative phases for video assessments.

Assessment	Critical portions of the operation	Rationale
Technical skills assessment	Performance of distal arterial and venous anastomoses (exposure is completed → last suture is cut after tying) Performance of proximal arterial anastomosis (initial use of electrocautery to isolate the area for anastomosis → last suture is cut after tying)	Video segment would contain technical skills (eg, economy of motion: creation of anastomosis) that are critical for a successful operation.
Nontechnical practices assessment	Preinduction verification (prior to → end of discussion) Preincision timeout (prior to → end of discussion) Prebypass transesophageal echocardiography (TEE) assessment (surgeon request for TEE → completed discussion between the surgeon and anesthesiologist) Preparation and weaning from bypass (surgeon requests the heart to be filled up → protamine finished)	Video segment would contain nontechnical practices (eg, decision making and communication/teamwork: discussion during the verification and timeout, as well as focusing on ensuring a safe weaning from cardiopulmonary bypass).

#### Hospital Performance Feedback

The DCC will provide monthly reports to hospitals, including number of digitally recorded operations, quality of transmitted digital recordings, and adherence to study operational protocols.

#### Peer Assessment Module

We will use a two-stage process for recruiting candidate assessors as follows: (1) we will poll the Michigan Society of Thoracic and Cardiovascular Surgeons Quality Collaborative (MSTCVS-QC), MPOG, and the Michigan Perfusion Society membership for potential assessors working outside of Michigan or at hospitals not participating in MPOG, and (2) if unable to secure sufficient assessors, we will recruit from the MSTCVS-QC, MPOG, and Michigan Perfusion Society membership.

Assessors, blinded to the hospital and operative team, will provide technical (aim 1) and nontechnical (aim 2) video-based assessments of cardiac surgical operations using a web-based Health Insurance Portability and Accountability Act (HIPAA)-compliant assessment platform.

Each operation will receive at least 12 assessments (three for each provider group), with 20% of assessments rereviewed. Surgeons will assess a surgeon’s (1) technical skills (modified OSATS plus cardiac surgery–specific skills) via a validated 5-point behaviorally anchored scale and (2) nontechnical practices using NOTSS [13]. Anesthesiologists will use ANTS [14], scrub nurses will use SPLINTS [15], and perfusionists will use PINTS for nontechnical assessments (all nontechnical taxonomies will use an 8-point ordinal scale). Segments will capture each operation’s critical phases. Technical skill assessors will be given one operative field camera angle (Cam Surgical Field [SF]) for their assessment (Figure 2). Given the interdependence of intraoperative team members, nontechnical assessors will be provided alternative camera angles depicting the intraoperative team (Cam Operative Team [OT] #1 and #2). Assessors will receive an Amazon coupon for completed reviews.

We will resubmit 20% of edited segments to the same (test-retest reliability) or other assessors (interrater reliability) using an intraclass correlation coefficient α ≥.670 for good concordance [28].

#### e-Learning Training Module

We will use a web-based training and readiness module that will include (1) foundational knowledge of the relevant tool and (2) video examples of correct identification, categorization, and assessment. Assessors will have to reach 70% agreement with gold standard (investigative team) assessments to contribute to the study. A median 70% agreement with reference assessments will serve as a basis for assessor eligibility to conduct real case assessments [29].

#### Clinical Complications

We will calculate each surgeon’s adverse event rate for the previous 2 years using each hospital’s Society of Thoracic Surgeons (STS) data.

### Aim 1: Investigate the Relationship Between Peer-Rater Assessments of a Surgeon’s Technical Skills and Variability in Risk-Adjusted Patient Adverse Events

#### Approach

We will conduct peer-reviewer assessments of recorded CABG operations at six MPOG hospitals (representing 36 surgeons) to associate technical skills with major adverse events.

Each surgical operation will be divided (using our video segmentation protocol) into prespecified phases containing the most critical operative portions. The DCC will distribute video segments for surgeon assessment via our HIPAA-compliant assessment platform that will provide assessors with a view of the operative field (from Cam SF, Figure 2). Surgeon assessors will provide domain-specific and overall summary judgements (using a modified OSATS taxonomy). Twenty percent of segments will be resubmitted for review to test assessor reliability. We will associate the average assessments with the adjusted risk of major morbidity and mortality over the prior 2 years for each surgeon.

#### Measures

Our primary exposure will be the average summary assessment of each surgeon’s technical skills. The primary outcome will be a surgeon’s STS composite major morbidity or mortality (ie, permanent stroke, surgical re-exploration, deep sternal wound infection, renal failure, prolonged ventilation, or operative mortality) rate. We will use clinical data from each center to adjust for covariates incorporated within the STS risk prediction models [30,31].

#### Analytical Plan

We will use linear mixed effect models to model assessments of surgical procedures where assessors and surgeons are included as random effects. We will quantify variation in peer-assessor assessments of a surgeon’s technical skills and use the intraclass correlation coefficient to measure interassessor reliability. We will use predictions of each surgeon’s technical skills from the linear mixed effect models as summary measures of a surgeon’s technical skills in subsequent analyses. Generalized linear mixed effect models with a logit link will then be used to associate a surgeon’s technical skills with our composite outcome. We will model surgeons and hospitals as random effects, accounting for the nesting structure of the data (ie, patients nested within surgeons and hospitals). We will adjust for patient and surgeon factors by including them as fixed effects in the models. The factors of interest are summary measures of a surgeon’s technical skills, which are included as surgeon-level explanatory variables. We will consider the overall assessments of a surgeon’s technical skills, averaged across three assessors and each domain individually.

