#### Power Analysis

We use simulations to evaluate statistical power for a two-sided test (α=.05). Our analysis will be based on outcomes for approximately 7200 operations over 2 years from 36 surgeons (approximately 100 operations per surgeon) at six hospitals. We estimate having approximately 98% power in detecting an odds ratio of 0.85 per one unit (standardized) increase in a surgeon’s technical skills for the rate of adverse events.

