#### Measures

Our primary exposure will be the average summary peer assessment of each provider’s nontechnical practices. Similar to aim 1, the primary outcome will be the rate of major morbidity or mortality, adjusting for clinical covariates [30,31].

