#### Analytical Plan

We will use generalized linear mixed effect models with a logit link to associate peer-assessor assessments of nontechnical practices of the surgeon with the surgeon’s STS composite score for major morbidity and mortality. Models will be similar to those described in aim 1, although we will include average summary measures of surgeon’s nontechnical skills as surgeon-level explanatory variables and hospital-level average summary measures of anesthesiologists, perfusionists, and scrub nurses. Both overall summary measures and individual scale domains will be considered. We will focus primarily on assessing the effects of nontechnical practices on morbidity and mortality rates, while adjusting for patient-level risk factors and a surgeon’s technical skills. We will explore the influence of nontechnical practices on the relationship between a surgeon’s technical skills and our composite endpoint by including nontechnical practices as an interaction term in models with technical skills.

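### Aim 2 counts three hospital-level team averages among its primary exposures, but six hospitals leave 2 degrees of freedom, too few to test them reliably at two-sided .05

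*Protocol article*

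**What the plan says.** The protocol article fixes the following.

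- **Aim 1, Analytical Plan.** "Generalized linear mixed effect models with a logit link will then be used" to relate technical skill to the composite outcome. "We will model surgeons and hospitals as random effects", and the skill summaries are covariates, "which are included as surgeon-level explanatory variables". Patient and surgeon factors are further fixed effects; the number of surgeon factors is not given.
- **Aim 1, Power Analysis.** "We use simulations to evaluate statistical power for a two-sided test (α=.05"), based on "approximately 7200 operations over 2 years from 36 surgeons (approximately 100 operations per surgeon) at six hospitals". The claim is "approximately 98% power in detecting an odds ratio of 0.85 per one unit (standardized) increase" in technical skill.
- **Aim 2, Measures.** "Our primary exposure will be the average summary peer assessment of each" provider, with no ranking of the provider groups.
- **Aim 2, Analytical Plan.** The models resemble those of Aim 1. They contain the surgeon's nontechnical score at surgeon level, adjustment for technical skill, and "hospital-level average summary measures of anesthesiologists, perfusionists, and scrub nurses".
- **Aim 2, Power Analysis.** Power is called sufficient for the Aim 1 effect sizes because the surgeon's nontechnical score is a surgeon-level variable. The three hospital-level terms are not mentioned.

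The article does not name the test statistic, the estimation method or the degrees of freedom for the fixed effects. It neither plans nor rules out a small-sample correction.

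**The concern.** Each hospital average takes only six distinct values, so its evidence comes from six hospitals, however many of the 7200 operations lie beneath them. Three such covariates plus an intercept use four of the six hospital-level degrees of freedom. The remaining two must supply the estimate of between-hospital variation.

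The article still counts these scores among the primary exposures of an aim described as team-based, and the only alpha it mentions is .05. A spurious team effect could then be reported as a primary result. The Results section says that findings will feed coaching interventions, so such an error would have consequences. Conversely, a properly calibrated test would very probably miss a real effect, and a null result would carry little information.

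**Working it through.** **Inputs from the article:** 7200 operations, 36 surgeons, 6 hospitals; two-sided .05; odds ratio 0.85 per standardized unit; stated power 98%. 7200/36 = 200 operations per surgeon; the stated 100 or so fits if read as per year. Both values were tried.

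**Assumed, because the article does not give them:** surgeon SD 0.1–0.3 and hospital SD 0.1–0.4 on the logit scale; event rate 15% or 35% (35% is in the Introduction; the power paragraph gives none); six surgeons per hospital.

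**1. The plan's own figure.** For a surgeon-level exposure, power = Φ(|ln 0.85|/SE − 1.96), with SE² = [SD² + 1/(m·p(1−p))]/36 and |ln 0.85| = 0.1625.
- p = 0.35, m = 200, SD 0.19: SE² = (0.0361 + 0.0220)/36, SE = 0.0402, power = Φ(4.05 − 1.96) = 98%.
- p = 0.15, m = 200, SD 0.14: SE² = (0.0196 + 0.0392)/36, SE = 0.0404, power = 98%.

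The 98% therefore cannot be derived from the stated inputs alone, but it is attainable. Simulated power was 99.3% (rate 35%, surgeon SD 0.15), 98.5% (15%, both SDs 0.1), 96.1% (35%, SD 0.2) and 80% (35%, SD 0.3).

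**2. Hospital terms, large-sample test.** Residual degrees of freedom: 6 − 1 − 3 = 2. P(|t| > 1.96) on 2 df is 18.9%. Maximum likelihood also divides by 6 instead of 2. If hospital variance dominates, the cut-off becomes 1.96 × √(2/6) = 1.13 and the rejection rate is 37.5%.

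Simulation under no effect (logit mixed model, Laplace maximum likelihood; 3000 runs per scenario for Wald z without added covariates, 2500 for likelihood ratio and for added covariates):

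| Term | Wald z | Likelihood ratio |
|---|---|---|
| Aim 2 hospital averages, each | 13–36% | 23–24% |
| At least one of the three | 32–60% | not run |
| Aim 2 surgeon terms | 6.7–9.4% | about 8% |
| Aim 1 surgeon term | 6.4–7.2% | 6–7% |

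The likelihood-ratio column covers surgeon SD = hospital SD = 0.2 only. With three added surgeon covariates the Aim 1 rate under z was about 9%. With those covariates plus the planned interaction, Aim 2 surgeon terms reached 11–12%.

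**3. Hospital terms, t reference on 2 df.** The critical value is 4.30. An approximate power uses hospital-level variance v = hospital SD² + surgeon SD²/6 + 1/(1200·p(1−p)), with 1200 = 7200/6. A standardized covariate keeps about 6 − 1 − 2 = 3 units of sum of squares after the intercept and the other two averages, so SE = √(v/3). Noncentral t on 2 df with noncentrality 0.1625/SE gives:

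| Surgeon SD, hospital SD, rate | SE | Noncentrality | Power |
|---|---|---|---|
| 0.1, 0.1, 35% | 0.071 | 2.27 | 26% |
| 0.2, 0.2, 35% | 0.129 | 1.25 | 12% |
| 0.2, 0.4, 35% | 0.238 | 0.68 | 7% |

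The t reference does not fully calibrate a maximum-likelihood fit either. Null rejection for hospital terms was 0.1–5.4% in most scenarios, but 9–10% at hospital SD 0.4.

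**4. Surgeon terms, t reference.** Without surgeon covariates: 5.4–6.3% in Aim 1 (29 df) and 5.4–8.3% in Aim 2 (28 df).

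**The case against.** The strongest objection is that the inflated rates belong to uncorrected z or likelihood-ratio inference, which the article does not specify. The reference distribution and degrees of freedom are normally set in the statistical analysis plan, which is not shown, and a condensed article may omit them. This stands for the surgeon-level terms. A reader might infer that the Aim 1 test fails to hold 5%. The article does not support that: it names no such test, and even an uncorrected one would add only 1–2 points unless several surgeon covariates are added or skill clusters strongly by hospital. A reader might also infer that the stated 98% power is inflated. That is not shown either: the simulated test is not described, and 98% is attainable.

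The objection does not rescue the hospital terms. The model and the number of hospitals are fixed in the article, and the choice of test only exchanges false positives for lack of power.

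A second objection is that the Aim 2 Analytical Plan opens with the surgeon's nontechnical practices, and the power statement argues only from that score, so the hospital averages may be meant as secondary. That is a reasonable guess at intent, but the Measures section says otherwise and the passages need to be reconciled.

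A third is that the Limitations section allows for adding hospitals. This is a contingency tied to low hospital variability or too few recordings, and the stated design remains six.

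**Conclusion.** The concern holds for the three hospital-level averages in Aim 2. With 2 hospital degrees of freedom they cannot be tested reliably at two-sided .05: about 13–36% false positives per term under uncorrected z and 23–24% by likelihood ratio where tried, or roughly 7–26% power for an odds ratio of 0.85 under a 2-df t reference. The ranges depend on the assumed variance components and event rates; the count of 2 degrees of freedom does not. The Aim 2 claim of sufficient power covers only the surgeon-level score.

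For surgeon-level terms the point is minor and conditional: about 6–7% in Aim 1 and 7–9% in Aim 2 if no small-sample method is used, and more with several surgeon covariates. It is a reason to state the method, and it does not show that the planned test is invalid.

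**What to change.** Main changes, all to wording:

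- **Aim 2, Measures:** name the surgeon's nontechnical score as the single primary exposure.
- **Aim 2, Analytical Plan:** report the anesthesiologist, perfusionist and scrub nurse hospital averages descriptively, without significance claims.
- **Aim 2, Power Analysis:** limit the statement to the surgeon-level score.

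Secondary change, to both Analytical Plans: test surgeon-level terms with a REML-type fit and a t reference whose degrees of freedom account for all surgeon-level and hospital terms in the model, or with a parametric bootstrap. Use the same test in the power simulation. The degrees of freedom should not be fixed before the surgeon factors are listed.

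Cost: there would be no formal test of the hospital-level team averages, which six hospitals cannot support anyway. For surgeon terms, the REML-type fit with a t reference lowered power by about 3–7 points in simulated cases (for example 90% to 87%, 68% to 61%). Changing only the reference distribution cost 1–3 points (96.1% to 95.1%, 80.2% to 77.6%). No new data are needed.
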